**Figure 1 F1:**
[figure not shown]
**MOTAP study schema and study outline.** IV, intravenous; MOTAP, medial open transversus abdominis plane; PCA, patient-controlled analgesia.

### Interventions

#### Preoperative care (both groups)

All patients will undergo routine preoperative testing at the preadmission clinic to confirm fitness for surgery (medical history, electrocardiogram, blood work, and so forth). No additional tests are required beyond standard-of-care for patients undergoing liver resection.

#### Intraoperative care (both groups)

Patients will undergo routine anaesthesia and liver surgery with no additional requirements for this study. No preoperative oral analgesics are permitted, including non-steroidal anti-inflammatory drugs, gabapentin, and acetaminophen. Epidural catheters, intravenous lidocaine, and ketamine are not permitted. Surgery will be performed through a right subcostal incision. An upper midline extension or limited left subcostal extension is permitted. All aspects of the liver resection will be left to the surgeon’s discretion. Local anaesthetic may not be infiltrated into the surgical wound.

#### Insertion of MOTAP catheters (both groups)

Following liver resection, the operating surgeon will insert two catheters. The following muscles will be identified: rectus abdominis, transversus abdominis, internal oblique, and external oblique. The surgeon will dissect between the internal oblique and transversus abdominis fascia superiorly to open the TAP. A plane will also be developed between the rectus muscle and the posterior sheath. The first catheter will be placed subcostally in the anterior axillary line, between the transversus and internal abdominal muscles. The second catheter will be sited at the lateral border of the right rectus abdominis muscle, between the posterior rectus sheath and the rectus abdominis muscle. Approximately 10 cm of catheter will be left in each plane, and tunnelled to skin sites distal to insertion. The catheters will be secured under occlusive sterile dressing, and covered with tape. The skin will be closed using either staples or suture at the surgeon’s discretion. The catheter will be fastened to the skin using steri-strips and an occlusive sterile dressing. For the TAP catheter we will use the 001159-20D InfiltraLong 600 T (manufacturer Pajunk, Germany) and we will use a standard three-orifice catheter for the rectus space.

The study lead at each site will be responsible for ensuring that all participating surgeons adhere to this technique of MOTAP insertion. Prior to enrolling a patient, each participating surgeon must perform at least one MOTAP insertion with the site’s lead present to become credentialed in the technique. We will audit the insertion technique of each surgeon at least every five cases to ensure consistency.

#### Experimental group - local anaesthetic infusion through MOTAP

At the conclusion of surgery, both catheters will be bolused with 20 ml ropivacaine 0.2% followed by a continuous infusion through each catheter of ropivacaine 0.2% 5 ml per hour.

#### Control group – normal saline infusion through MOTAP

At the conclusion of surgery, patients in the control group will have 0.9% normal saline 20 ml bolused then a 5 ml/hour infusion into each catheter.

#### Postoperative care (both groups)

Patients in both groups will be prescribed celecoxib 200 mg orally twice daily (if baseline serum creatinine is less than 90 μmol/l), and IV PCA hydromorphone 0.2 mg bolus with a lockout time of 5 minutes and no background infusion. If patients have inadequate analgesia with this regimen the bolus dose will be increased to 0.2 to 0.4 mg bolus and the TAP catheter infusions will be increased to 7.5 ml/hour in each catheter. If pain is still inadequately controlled, patients will be started on a continuous intravenous infusion of hydromorphone 0.2 mg/hour in addition to the bolus PCA dosing. If pain is still inadequately controlled, the study coordinator will be contacted and the patient assessed by the study site lead.

Patients may receive additional opioid boluses to control acute intractable pain while the IV PCA dose is being adjusted, at the discretion of the acute pain service clinician or the post-anaesthesia care unit nurse caring for the patient. These doses will be recorded and included in the measurement of total opioid consumption.

Serum creatinine will be monitored daily in the postoperative period and, if it increases above 90 μmol/l, the celecoxib will be discontinued; however, patients will remain in the trial.

The MOTAP catheters will be removed on the morning of postoperative day 3 in all patients.

### Blinding

This will be a blinded, placebo-controlled study. All patients, clinicians, and data collectors will be unaware of the group allocation. A pharmacist not involved in patient care will dispense the study medications according to the computer-generated randomization list.

### Outcome assessment

#### Primary outcome

The primary endpoint is mean cumulative postoperative opioid consumption over the first 2 postoperative days (48 hours). Both IV PCA opioids and oral opioids will be recorded from the patient’s medical records daily, converted to morphine equivalents, and compared between the two groups.

The following information will be collected at regular intervals as a measure of the primary endpoints: cumulative IV PCA opioid consumption every 12 hours for 72 hours as well as total opioid consumption for the entire hospital stay.

#### Secondary outcomes

We will collect the following secondary patient-reported outcome scores:

1. NRS
[30] scores for pain at rest and with coughing (0 = no pain, 10 = worst possible pain) three times daily (TID) for 48 hours and then daily until discharge.

2. Preoperative Current Pain and Pain History Questionnaire, NRS for Pain Intensity and Pain Unpleasantness, PCS
[31], SF-MPQ-2
[32,33], Pain Disability Index (PDI)
[36,37], and HADS
[34] at baseline.

3. NRS patient satisfaction scores regarding pain control (0 = totally satisfied, 10 = totally dissatisfied) TID for the first 48 hours and then daily until discharge.

4. NRS for Pain Intensity and Pain Unpleasantness, PCS
[31], SF-MPQ-2
[32,33], and HADS
[34] on the day of discharge.

5. Long-term pain Follow-Up Pain Questionnaire, PDI
[36,37], PCS
[31], SF-MPQ-2
[32,33], HADS
[34], and The Follow-Up Questionnaire 6 months following surgery (via a routine follow-up telephone call).

6. In-hospital opioid-related side effects - presence of nausea, vomiting, pruritus, and dizziness (assessed TID for the first 48 hours, then daily until discharge).

7. Sedation scores, measured TID for the first 48 hours, then daily until discharge using a standard sedation scale (0 = alert, 1 = mild (occasionally drowsy, easy to arouse), 2 = moderate (frequently drowsy, easy to arouse), 3 = severe (somnolent, difficult to arouse), S = normal sleep, easy to arouse).

8. Duration of hospital stay.

9. Time to first bowel movement.

10. Time to ambulation.

11. Incidence of in-hospital complications, graded using the Clavien classification
[38].

### Criteria for removal from study

If, at any time, the patient is found to be ineligible for the protocol as designated in the section on eligibility the patient will be removed from the study. Patients who are not extubated within 4 hours from the end of the operation or who are reintubated within 48 hours from the end of the operation (including a return to the operating room) will also be excluded from the primary analysis, although we will continue to follow them while in hospital. Patients who wish to withdraw from the study at any point in time will be able to do so.

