### Intravenous opioid patient-controlled analgesia

Despite the variety of pain-relieving modalities available, postoperative pain following liver surgery is significant and remains a challenge to manage. Opioid analgesia, while effective at rest, fails to provide adequate pain relief associated with movement such as breathing, coughing, ambulation, and gastrointestinal motility
[11,31]. Moreover, opioids are associated with adverse effects such as nausea, vomiting, constipation, sedation, and respiratory depression
[20].

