## Methods/design

### Study design

This is a multicentre, prospective, blinded, randomized controlled trial comparing MOTAP catheters plus IV PCA to standard care (IV PCA alone) in patients undergoing subcostal incision for liver resection. Full inclusion and exclusion criteria for the trial are summarized in Table 
1. The trial has been approved by the Toronto Academic Health Sciences Network Research Ethics Boards from Sunnybrook Health Sciences Centre (178–2013) and from the University Health Network (12-0493-A).

**Table 1 T1:** MOTAP study inclusion and exclusion criteria

**Inclusion criteria**	**Exclusion criteria**
• >18 years of age	• Patients unable to comprehend instructions, consent, or co-operate with pain assessment
• Undergoing liver resection using a subcostal incision (upper midline extension is allowed)	
• Incision extends to allow visualization of internal oblique and transversus abdominis muscles	• Allergy to any study medications
	• Patient not able to be extubated postoperatively for any clinical reason
	• Laparoscopic surgery
	• Co-existing epidural or intrathecal analgesia
	• Chronic pain disorders or on long-term opioids (greater than 1 month prior to operation)
	• History of substance or alcohol abuse
	• Transplant donor liver resections
	Prior right subcostal incision

MOTAP, medial open transversus abdominis plane.

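### Patients extubated late or reintubated within 48 hours are excluded from the primary analysis after randomised treatment has started, which opens the comparison to selection bias

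*Protocol article*

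**What the plan says.** Under Criteria for removal from study, the protocol article sets two rules.

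- **Ineligibility.** "If, at any time, the patient is found to be ineligible for the protocol", as defined in the eligibility section, the patient is removed from the study.
- **Airway events.** Two groups are dropped from the main result. The first is described as "Patients who are not extubated within 4 hours from the end of the operation". The second group is made up of those "who are reintubated within 48 hours from the end of the operation". What happens to both is given at the end of the same sentence, after an opening parenthesis: "including a return to the operating room) will also be excluded from the primary analysis". Follow-up of these patients is then promised for the hospital stay only.

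Table 1 (Study design) also lists as an exclusion criterion: "Patient not able to be extubated postoperatively for any clinical reason".

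On timing, the experimental-group section states: "At the conclusion of surgery, both catheters will be bolused with 20 ml ropivacaine 0.2"% (per cent sign added). The control-group section gives the saline bolus at the same moment. The Blinding section has a pharmacist dispense by the randomisation list. The primary endpoint is cumulative opioid use over 48 hours, compared by a two-sided t-test. The article states no analysis of all randomised patients.

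**The concern.** The 4-hour and 48-hour criteria run from the end of the operation, and the randomised bolus is given at the end of surgery. Whether a patient meets either criterion is therefore known only after allocation and, as planned, after treatment has begun. The 48-hour criterion also covers the same period as the endpoint.

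Such exclusions are harmless only if the event is unrelated to treatment, and the article's own reasoning does not allow that assumption for reintubation. Its section on intravenous patient-controlled analgesia says that "opioids are associated with adverse effects such as nausea, vomiting, constipation, sedation, and respiratory depression". Its Background says that pain from a subcostal incision may lead to respiratory complications. The trial is run because the catheters are expected to reduce both opioid use and pain. If they do, reintubation may be less frequent, or may occur in different patients, in the experimental arm. The retained patients would then no longer be the groups that randomisation formed.

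**Working it through.** **1. Order of events.** The moment of randomisation is not stated, but it must precede the bolus because syringes are dispensed by the allocation list. The order is: allocation, bolus at end of surgery, extubation check at 4 hours, reintubation check to 48 hours, endpoint complete at 48 hours.

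**2. The plan's own figure.** The sample size section gives a control mean of 39.09 mg, SD 25.07, a 40% reduction, two-sided alpha 0.05 and 90% power.

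- Difference = 0.40 × 39.09 = 15.64 mg; experimental mean = 0.60 × 39.09 = 23.45 mg.
- n per group = 2 × 25.07² × (1.960 + 1.282)² / 15.64² ≈ 54.0, so 55. The exact noncentral-t calculation gives 56.
- The stated 58 is within 2 or 3 patients of this. Power by the t-test is 91.5% at 58 and 92.3% at 60 per arm.

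**3. Loss of numbers alone.** If 10% were excluded in each arm with no bias (54 per arm), power would be 89.5%. Lost sample size is not the main problem.

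**4. Shift in the estimate.** The article gives neither exclusion rates nor the opioid use of excluded patients, so every rate below is an assumption. If a fraction p with mean x is removed from an arm with mean m, the retained mean is (m − p·x)/(1 − p).

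| Excluded, control / experimental | x | Retained means | Difference |
|---|---|---|---|
| none | – | 39.09 / 23.45 | 15.6 mg |
| 10% / 3% | 80 mg | 34.54 / 21.71 | 12.8 mg (18% lower) |
| 5% / 2% | 80 mg | 36.94 / 22.30 | 14.6 mg |
| 5% / 2% | 20 mg | 40.09 / 23.52 | 16.6 mg |

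With 60 per arm, 10% and 3% are about 6 and 2 patients.

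**5. Power in the 10% / 3% case.** About 54 and 58 patients remain.

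- *SD held at 25.07.* Noncentrality = 12.84 / (25.07 × √(1/54 + 1/58)) = 2.71; power about 77%.
- *SD made consistent.* If 25.07 is the SD of the full arm, removing a distant subgroup shrinks the retained SD s. It follows from 25.07² = (1 − p)s² + p·sx² + p(1 − p)(x − r)², where r is the retained mean and sx the SD among the excluded.
  - sx = 0: s = 22.2 (control) and 23.4 (experimental), pooled 22.8; noncentrality 2.98; power about 84%.
  - sx = 25.07: s = 20.5 and 22.9, pooled 21.8; noncentrality 3.11; power about 87%.

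**6. Under no treatment effect.** If excluded patients exceed retained ones by D mg in both arms and the full-arm means are equal, bias = (difference in exclusion rates) × D.

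| Excluded, one arm / other | D | Bias | Type I error |
|---|---|---|---|
| 5% / 5% | any | 0 | 0.050 |
| 5% / 10% | 20 mg | 1.0 mg | 0.055 |
| 5% / 15% | 20 mg | 2.0 mg | 0.069 |
| 5% / 15% | 39 mg | 3.9 mg | 0.126 |

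**The case against.** The strongest reply is that the rule is pre-specified, objective and applied blind, and that opioid use in a ventilated patient is a different quantity. The endpoint is meant to capture patients titrating their own analgesia. Opioid given by staff to an intubated patient is partly for sedation, and a few extreme values could dominate a mean with 60 per arm. This stands as a reason to report the restricted analysis as well. It does not make the restricted set the right primary one: blinding stops staff from excluding selectively, but it does not stop treatment-related events from selecting patients.

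A reader might infer more than the text supports:

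- **Return to theatre as its own ground.** The parenthesis follows the reintubation clause and most naturally covers reintubation for a return to the operating room. A separate ground is not clearly stated.
- **All ineligibility removals as post-treatment.** Some Table 1 items, such as laparoscopic surgery or an incision that does not expose the muscles, are known before the bolus. Only removals made after study drug has started raise this concern, and it is the lesser one.
- **Every airway exclusion as opioid-driven.** The respiratory-depression argument fits reintubation. For non-extubation at 4 hours, the anaesthetic and the operation are the more obvious drivers. Nor does the article say that excluded patients have the worst opioid-related outcomes.
- **Power falling to 77%.** That requires the SD to stay at 25.07 after patients far from the mean are removed. With a consistent SD it is about 84–87%.

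**Conclusion.** The concern holds for late extubation and reintubation. The article explicitly fixes a primary analysis set that depends on events seen after randomised treatment has begun and inside the endpoint window, and nothing else in it corrects this. For reintubation, the article itself supplies the reasons why treatment could matter.

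Size and direction are unknown. On assumed rates, the 15.6 mg difference moves to between 12.8 and 16.6 mg, so the bias can go either way. Under no effect, type I error ranges from 0.050 with equal exclusion to 0.126 in the most extreme case tried. These figures show sensitivity and do not predict what will happen in this trial.

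There is also a smaller inconsistency. Under Table 1 and the first removal rule, a patient who cannot be extubated is ineligible and removed from the study. The next sentence keeps a late-extubated patient under follow-up, but states this only for the hospital stay, although the secondary outcomes include a 6-month assessment. The second sentence may be meant as the working form of the Table 1 criterion, but the article does not say so and the passages must be reconciled.

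**What to change.** - Make the primary analysis all randomised patients in the arm assigned, using all opioid recorded to 48 hours. If patients who never received study drug are to be left out, the minimum is everyone in whom it was started.
- Keep the present exclusions as a labelled sensitivity analysis. This addresses opioid given for sedation during ventilation.
- Report exclusions by arm and by reason.
- Continue these patients to the 6-month follow-up.
- Reconcile the Table 1 non-extubation criterion with the removal section, so that it is clear which patients leave the study and which leave only one analysis.

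Delaying release of the allocation to the end of resection would not help here, because the 4-hour and 48-hour events come later still.

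The cost is mainly wording, to be settled before unblinding. These patients are already followed in hospital and opioid use is taken from medical records, so the 48-hour data should be obtainable. The 6-month contact is a small addition. The statistical cost is some extra variance, and possibly outliers, from ventilated patients; its size cannot be judged from the article.

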### Data analysis

All statistical analyses will be performed using SAS software version 9.2 (SAS Inc., Cary, NC, USA). All tests will be two-sided and significance will be considered at *P* < 0.05.

#### Primary analysis

Mean cumulative postoperative opioid consumption during the first postoperative 48 hours will be reported for the two groups as mean ± standard deviation. The two groups will be compared using a two sided *t*-test.

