### Recruitment

Patients meeting the eligibility criteria will be recruited at the preoperative surgical consent visit or the anaesthesia pre-assessment clinic. Information pamphlets will be provided and written informed consent will be obtained. At the time of enrolment, patients will complete baseline questionnaires: the ‘Preoperative Current Pain and Pain History Questionnaire’, Numeric Rating Scale (NRS)
[30] for Pain Intensity and Pain Unpleasantness, the Pain Catastrophizing Scale (PCS)
[31], the McGill Pain Questionnaire - Short Form-2 (SF-MPQ-2)
[32,33], and the Hospital Anxiety and Depression Scale (HADS)
[34].

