### Randomization

Patients will be randomized to one of two parallel groups: experimental (local anaesthetic through MOTAP catheter) or placebo (normal saline through MOTAP catheter). Each research pharmacy will have a concealed randomization list and the appropriate syringes will be dispensed by the pharmacy. The code will be retained centrally and only revealed to the investigators once recruitment and data collection is completed. Randomization will be stratified by centre. A brief schema and study outline of this trial is summarized in Figure 
1.

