#### Secondary outcomes

Outcomes will be reported for the two groups as mean ± standard deviation for normally distributed variables and the median and interquartile range for nonparametric variables. The two groups will be compared using chi-square tests, two sample Student’s *t*-test or the Wilcoxon rank-sum test as appropriate. Time-to-event outcomes will be defined from the completion of surgery until the time of event. Patients who do not have the event at last follow-up will be censored. The number of censored events is expected to be low as both events (ambulation and bowel movements) are requirements prior to the patient’s discharge from hospital. Time to event outcomes will be analyzed using the Kaplan-Meier method and survival curves will be compared between the two groups using the log-rank test.Sample size calculation

Our pilot data consisted of 111 patients that had undergone liver resection surgery between April 2004 and January 2009 prior to the use of MOTAP catheters when postoperative pain relief was provided by IV PCA hydromorphone alone. Cumulative hydromorphone consumption over the first 48 hours after surgery was 39.09 ± 25.07 mg. Based on our experience with the use of MOTAP catheters following adult liver donation surgery, we have found a reduction of 47% in mean cumulative opioid consumption over the first 2 postoperative days (48 hours). Patients receiving MOTAP catheters consumed a mean ± SD of 20.81 ± 15.8 mg of hydromorphone. The difference of approximately 18 mg over 48 hours is clinically significant and represents a reduction of almost 50%.

To be conservative, we will estimate a relative reduction in mean cumulative opioid consumption of 40%. Assuming a baseline opioid consumption of 39.09 mg with a standard deviation of 25.07, a sample size of 58 patients per group will achieve 90% power at a significance level (alpha) of 0.05. We will round up to 120 patients in total (60 patients in each group).

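### Randomization is stratified by centre but the primary t-test ignores centre, so it is conservative if centres differ in opioid use; available baseline adjustment is also unused

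*Protocol article*

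**What the plan says.** Under Randomization, the article states: "Randomization will be stratified by centre". Study design calls the trial multicentre and names two institutions whose ethics boards approved it.

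Under Primary analysis, cumulative opioid consumption over 48 hours is summarized by group, and then "The two groups will be compared using a two sided" t-test. Neither that section nor the opening of Data analysis, which sets two-sided tests at P < 0.05, mentions centre or a covariate.

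Baseline information is nonetheless available. Under Recruitment: "At the time of enrolment, patients will complete baseline questionnaires". These cover pain history, NRS pain intensity and unpleasantness, PCS, SF-MPQ-2 and HADS; the Secondary outcomes list adds the PDI. Baseline creatinine must also be known, because under Postoperative care celecoxib is prescribed "if baseline serum creatinine is less than 90" μmol/l.

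The sample size text, printed at the end of Secondary outcomes under Data analysis, is built on the unadjusted comparison: "Assuming a baseline opioid consumption of 39.09 mg with a standard deviation of 25.07", a 40% reduction, and "a sample size of 58 patients per group will achieve 90% power at a significance level (alpha) of 0.05", rounded up to 60 per group.

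**The concern.** Stratifying by centre balances the arms within each centre, so a centre difference in opioid use no longer adds to the sampling variability of the treatment difference. A t-test that ignores centre estimates its error from the pooled spread, which still contains that difference. The reported standard error then exceeds the true one, the interval is too wide and the test rejects too rarely under the null. A centre difference is plausible here: anaesthesia is routine local practice, resection is at the surgeon's discretion, and discretionary opioid boluses count towards the endpoint.

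The baseline measures are a separate matter. Randomization is not stratified on them, so the t-test's standard error is correct without them. What is given up is extra precision that data already in hand might provide. That precision would matter most if the true effect were below 40%, a figure that rests on liver donors with catheters compared with earlier patients on IV PCA, not on a randomized comparison.

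**Working it through.** **Inputs from the article.** Control mean 39.09 mg; SD 25.07 mg, taken as common to both arms as the plan does; planned reduction 40%, so Δ = 0.40 × 39.09 = 15.636 mg; two-sided alpha 0.05; 60 per group.

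**Assumed, because the article gives no figures.** Two centres of equal size; a centre gap of δ SDs (0, 0.5 or 1); R², the share of outcome variance explained by baseline covariates (0 to 0.30).

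**The plan's own figure.** n per group = 2 × (25.07 × (1.960 + 1.282) / 15.636)² = 54.0, so 55 by the normal formula; the exact t calculation gives 56. The stated 58 is within two patients of the latter. Power by the t calculation is 91.5% at 58 and 92.3% at 60 per group. The planning standard error at 60 per group is 25.07 × √(2/60) = 4.58 mg.

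**Centre.** Two equal centres δ SDs apart add a variance of δ²/4 in SD² units. The article does not say whether 25.07 mg is a within-centre or an overall SD, so both readings are shown.

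- Within-centre SD: reported SE / true SE = √(1 + δ²/4).
- Overall SD: reported SE / true SE = 1 / √(1 − δ²/4).
- True alpha = 2 × [1 − Φ(1.96 × ratio)].
- Power of the unadjusted test = Φ((Δ − 1.96 × SE reported) / SE true); with a centre term, both SEs equal the true SE.

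| Gap | Reading of 25.07 | SE true | SE reported | Ratio | True alpha | Power, unadjusted | Power, centre term |
|---|---|---|---|---|---|---|---|
| 0 | either | 4.58 | 4.58 | 1.00 | 5.0% | 92.7% | 92.7% |
| 0.5 SD | within-centre | 4.58 | 4.72 | 1.03 | 4.3% | 91.9% | 92.7% |
| 0.5 SD | overall | 4.43 | 4.58 | 1.03 | 4.3% | 93.4% | 94.2% |
| 1 SD | within-centre | 4.58 | 5.12 | 1.12 | 2.8% | 89.0% | 92.7% |
| 1 SD | overall | 3.96 | 4.58 | 1.15 | 2.4% | 95.4% | 97.6% |

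These are normal approximations. Simulation with t critical values agrees to within a percentage point: at a 1 SD gap, about 88% against 92% on the within-centre reading and 95% against 97.5% on the overall reading.

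**Baseline covariates, with no centre gap.** Adjusted SE = 4.58 × √(1 − R²); power by the t calculation at 60 per group and Δ = 15.636 mg:

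| Assumed R² | SE (mg) | Power |
|---|---|---|
| 0 | 4.58 | 92.3% |
| 0.05 | 4.46 | 93.5% |
| 0.10 | 4.34 | 94.6% |
| 0.20 | 4.09 | 96.6% |
| 0.30 | 3.83 | 98.2% |

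**The case against.** The strongest reply is that nothing here is invalid. Under randomization the t-test is unbiased, any error in its level is on the safe side, it matches the unadjusted sample size calculation, and power at 60 per group is already about 92% on the plan's own inputs. All of that stands, and it limits the point to efficiency.

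The size of the effect is also uncertain. No centre gap is given, and with no gap the loss is nil. No correlation between any baseline score and opioid use is given either, and excluding chronic pain disorders, long-term opioid use and substance abuse may narrow the range of baseline pain and weaken it as a predictor. This also stands, which is why ranges are shown.

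A third reply is that covariate terms are often left to an analysis plan, which is not shown. This stands only in part. The article does not stay silent: it names the primary test, and that test does not follow the stratified design. If an analysis plan already includes centre, only the article's sentence and that plan need to be aligned.

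Three stronger readings are tempting but unsupported. A reader might infer that the type I error is below nominal as a matter of fact; this holds only if centres differ. A reader might infer that ignoring the baseline scores also makes the standard error wrong; it does not, because randomization was not stratified on them. A reader might infer that power falls below the planned 90%; among the cases shown this happens only with a 1 SD gap and 25.07 mg read as the within-centre SD, and the article does not settle that reading.

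**Conclusion.** The point holds in a conditional form. The stated primary test ignores the randomization stratum, and it is conservative to the extent that centres differ in opioid use. With two equal centres the effect is small at a 0.5 SD gap (standard error 3% too large, under one point of power). It is moderate at 1 SD: standard error 12 to 15% too large, alpha about 2.4 to 2.8%, and power about 88 to 89% against 92 to 93%, or about 95% against 97 to 98%, depending on which SD 25.07 mg represents. It is zero with no gap.

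The possible gain from baseline covariates is separate and rests wholly on an assumed R²: from 92.3% to between 93.5% and 98.2% power for R² of 0.05 to 0.30, and none at zero. The trial's conclusions would not be invalid as planned; they might be less precise than the collected data allow.

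**What to change.** Before unblinding, prespecify the primary analysis as a linear model of 48-hour opioid consumption on treatment, centre and a short named set of baseline covariates, for example baseline NRS pain intensity, PCS and baseline creatinine below 90 μmol/l. Use the baseline creatinine value, not celecoxib actually received, since celecoxib may be stopped after surgery. Report the adjusted mean difference with its 95% confidence interval, and keep the t-test as a sensitivity analysis. If only one change is made, add the centre term.

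The cost is analysis wording, including one line on how a missing baseline questionnaire is handled. No extra data, visits or patients are needed, and the sample size can stay as it is.
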